### Analysis

The same methods will be used to address the two research questions concerning the effectiveness of BIS and patient and carer distress and patient mastery of symptoms. Analyses will be presented separately for non-malignant and malignant participant groups. The baseline comparability of the arms will be examined by presenting pre-randomisation means and proportions of patient characteristics at timepoint t1 by randomised arm. The research questions will be addressed by cross-sectional comparison at t3 (end of intervention in fast track arm versus control condition in waiting list arm), using analysis of covariance adjusting for the baseline of the outcome within a linear regression framework. For the non-malignant group, this will be supported with the same analysis at t2.

Analyses will be primarily on an intention to treat basis. Secondary sensitivity analyses will be performed if there are deviations to the intervention protocol (requiring per protocol analysis) or there are baseline imbalances (requiring analysis adjustment). A graph will summarise the mean response over the time-points, with estimates and 95% confidence intervals for differences both between arms and within each arm over time from t3 to t5 (using paired t-tests). If a chi-squared test does not indicate that the t3 randomised effects are dissimilar in malignant and non-malignant groups, a simple average combined effect will be estimated with a narrower overall confidence interval to inform Phase IV. All analyses will be two-sided and assessed at the 5% significance level using SPSS software.

Qualitative data will be transcribed by an independent transcription company, checked and anonymised before analysis; transcripts will then be imported into NVivo software to facilitate the conduct of framework analysis [32]. Mixed method analyses will purposively sample qualitative data, based on quantitative findings.

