## Background

Intractable breathlessness can completely dominate a patient's life causing physical disability, loss of independence and dignity and lowered self-esteem [1-3]. It is common in advanced disease, both malignant and non-malignant. In chronic obstructive pulmonary disease (COPD) and heart failure it is nearly universal by the time of death, its prevalence reaching over 50% in both conditions in the advanced stages. It occurs in 49% of the general population with all cancers [4], and in 90% of those with lung cancer [5]; these figures will rise as deaths from mesothelioma peak in 2016 [6]. The incidence of breathlessness in cancer is second only to that of pain [7]. Breathlessness is also a devastating accompaniment in less common cardio-respiratory diseases, e.g. interstitial lung disease and cystic fibrosis. Despite its prevalence breathlessness remains a poorly controlled symptom in which traditional pharmacological interventions are frequently ineffective [1,8,9].

However, patterns of breathlessness in cancer and COPD differ. Once patients with cancer become breathless they usually have a very short time to live and may become breathless at rest, whereas patients with COPD may live with gradually worsening symptoms and increasingly devastating consequences for years. As a result, patients with different diagnoses and their carers may have different needs [10]. The effects on the patient and family with malignant or non-malignant disease include increased social isolation, reduced activity, chronic anxiety, loss of employment and other changes in roles and perceived status [3,11]. Further, the economic burden to the healthcare system is significant [12].

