### Sample size

Sample size was calculated using a power calculation, with the potential effect size and standard deviation informed by the existing literature and our Phase II trial [20]. The estimated standard deviation of the primary outcome measure is 2.5. In order to detect a 2-point difference in mean outcome between groups (equivalent to 0.8 sd effect size) with 80% power using a two-sided t-test at the 5% level of significance, it is necessary to analyse 26 patients per arm per disease group (trial) followed up with a primary outcome (total 104 patients). Therefore we propose to recruit a minimum of 120 patients, 60 per disease group, to ensure adequate power, effect size and allowance for attrition. Additionally, an adjustment for baseline in the analysis will improve the precision of the estimated intervention effect.

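### In the non-malignant group, separate t3 and t2 ANCOVAs leave patients with t2 but no t3 out of the primary contrast; a joint model would use them at almost no cost

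*Protocol article*

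**What the plan says.** The protocol article's Analysis section fixes the method. The effectiveness and distress questions are addressed by a cross-sectional comparison of arms at t3, using ANCOVA in a linear regression with the baseline value of the outcome as covariate. Then: "For the non-malignant group, this will be supported with the same analysis at t2". On the analysis population it says: "Analyses will be primarily on an intention to treat basis".

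Measurement points places t2 two weeks after t1 in the non-malignant sub-protocol. That is the mid-point of the intervention in the fast-track arm, while the other arm is still waiting; t3 follows at four weeks. The malignant sub-protocol has no t2.

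Sample size counts the patients to be analysed as those "followed up with a primary outcome (total 104 patients", that is 26 per arm per disease group. It allows for attrition by recruiting 60 per disease group.

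**The concern.** The t2 score is already collected and is likely to predict t3 well. The plan uses it only in a regression of its own, so it does nothing for the primary contrast when t3 is missing.

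Two things are at stake. The first is precision, because the t2 information on patients lost before t3 is discarded. The second is validity. A t3 regression on baseline alone relies on dropout being unrelated to t3 distress given arm and baseline. If patients leave in relation to their t2 distress, and the service has already moved t2 in the fast-track arm or patients leave for different reasons in the two arms, the remaining patients no longer give a fair comparison at t3.

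**Working it through.** **The plan's own figure.** Sample size gives: "The estimated standard deviation of the primary outcome measure is 2.5", a 2-point target difference, and the calculation "with 80% power using a two-sided t-test" at the 5% level. The normal approximation gives 2 × (1.960 + 0.842)² × (2.5/2)² = 24.5, so 25 per arm. By the exact noncentral t, 25 per arm gives 79.1% power and 26 gives 80.7%. The stated 26 reproduces and is not in question. The implied loss is 1 − 52/60 = 13.3%.

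**Assumptions, none given in the document.** Correlations r12 = 0.6 (t1-t2), r23 = 0.7 (t2-t3), r13 = 0.5 (t1-t3); 30 randomised per arm; all patients without t3 seen at t2 unless stated.

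**Precision, dropout unrelated to outcome.** Let m be the fraction without t3.

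- Variance of t3 explained by t1: R1² = 0.5² = 0.25.
- Explained by t1 and t2: R12² = (0.25 + 0.49 − 2 × 0.5 × 0.7 × 0.6)/(1 − 0.36) = 0.32/0.64 = 0.50.
- Large-sample variance, t3 only, relative to the unadjusted variance with no loss: (1 − R1²)/(1 − m).
- Joint use of t2: (1 − R12²)/(1 − m) + (R12² − R1²).

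| Loss m | t3 only | Joint | Variance reduction | Effective n per arm |
|---|---|---|---|---|
| 13.3% | 0.75/0.867 = 0.865 | 0.50/0.867 + 0.25 = 0.827 | 4.4% | 26.0 v 27.2 |
| 30% | 0.75/0.70 = 1.071 | 0.50/0.70 + 0.25 = 0.964 | 10% | 21.0 v 23.3 |

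Over wider assumptions (r13 0.3-0.5, r12 0.5-0.6, r23 0.5-0.8, half or all of the missing patients seen at t2), the t3-only standard error is 0.4% to 4.1% larger at 13.3% loss and 1.0% to 10.1% larger at 30%.

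**Bias, by simulation.** SD 2.5, correlations as in the table above, logistic dropout. Except in the first row, the service lowers distress by 1 point at t2 and 2 points at t3. Bias is towards no effect.

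| Dropout mechanism | Bias at 13.3% | Bias at 30% |
|---|---|---|
| Same in both arms, no t2 effect | about 0 | about 0 |
| Same in both arms, log-odds 0.4-0.8 per point of t2 | 0.04-0.08 | 0.06-0.13 |
| Follows t2 in the waiting-list arm only, log-odds 0.5 | about 0.16 | about 0.32 |

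Using t2 brings the bias to within about 0.02 points of zero in these scenarios.

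For scale, the standard error of the adjusted difference with 26 per arm is 2.5 × √0.75 × √(2/26) = 0.60. A bias of 0.08 is 0.08/0.60 = 0.13 of a standard error.

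**Where the joint model helps less.** If dropout depends on t3 itself (log-odds 0.4 per point, 13.3% loss), the bias is 0.125 for the t3 ANCOVA and 0.083 for the joint model. About two thirds remains (0.083/0.125 = 0.66).

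**The case against.** A baseline-adjusted ANCOVA at the end of the intervention is a valid, prespecified analysis. Over-recruitment covers the planned loss of numbers, and t2 is still reported. The correlations, t2 effects and dropout slopes are all assumed. A log-odds of 0.8 per point is steep: with an SD of 2.5 it is an odds ratio of exp(0.8 × 2.5) = 7.4 per SD. The interval from t2 to t3 is only two weeks, and nothing in the article shows that non-malignant patients leave because of t2 distress. All of this stands, and it keeps the point small.

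Four stronger readings are tempting, and the document does not support them.

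- *The analysis is stated to be complete-case.* The article does not say so. It is an inference from the cross-sectional t3 model and from the way the sample size is counted. Imputing t3 before the ANCOVA would be compatible with the wording.
- *The contrast is biased whenever dropout follows t2 distress.* It is not. With the same mechanism in both arms and no effect at t2, the bias cancels.
- *The plan omits missing-data sensitivity analyses, including for the malignant group.* An article commonly leaves these to the full protocol or analysis plan, neither of which is shown.
- *The Background's remark "Once patients with cancer become breathless they usually have a very short time to live" shows that attrition threatens this comparison.* It concerns cancer, the group without a t2 interview, so it says nothing about losses in the non-malignant group.

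What the objection does not remove is that the article itself chooses two separate regressions, and that a better use of t2 is available for the same estimand.

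**Conclusion.** The point holds as a cheap improvement to the non-malignant analysis; it is not a flaw that invalidates it. At the implied 13.3% loss the t3-only analysis gives up a few per cent of variance. Any bias is well under a tenth of the 2-point target, even when only waiting-list dropout follows t2 (0.16/2 = 8%). At 30% loss that last case reaches 0.32/2 = 16%, so the main value is protection if attrition exceeds the allowance.

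These sizes rest on the assumed correlations, on patients lost at t3 having been seen at t2, and on a mid-intervention effect or arm-specific dropout. Such an effect is plausible given the timing of t2, but the article gives no data on it. The gain shrinks if patients who miss t3 also miss t2.

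**What to change.** For the non-malignant group, replace the two ANCOVAs with one likelihood-based repeated-measures model: t2 and t3 as outcomes, t1-by-time and arm-by-time terms, and an unstructured covariance. Name the t3 arm contrast as primary and take the t2 contrast from the same model as supporting. The estimand is unchanged: the arm difference at t3, adjusted for baseline. Leave the malignant group's t3 ANCOVA as it is.

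The cost is wording in the analysis section and a slightly more complex model; no extra patients, visits or data are needed. The limits should be stated with it. The gain is confined to non-malignant patients who have t2, and the model relies on data being missing at random given t1, t2 and arm, so dropout driven by t3 itself is only partly corrected.

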### Cost-effectiveness

The cost of services used by each patient will be calculated from service activity data and appropriate unit costs. The BIS intervention costs will be based on staff salary costs, plus oncosts, overheads and equipment and divided by a relevant level of activity. Information on the use of other health and social services and informal care (proxy-valued as a homecare worker) will be collected with the Client Service Receipt Inventory (CSRI) [29]. This will be combined with appropriate unit cost data [e.g. [33]] to generate service costs. Cost comparisons will be made using bootstrapping methods to account for any skewness in data distribution. Cost-effectiveness will be assessed by combining cost data with that on the primary outcome measure (distress due to breathlessness) and quality-adjusted life years (QALYs), in the form of incremental cost-effectiveness ratios (if the intervention group has better outcomes and higher costs) and cost-effectiveness acceptability curves which will show the probability that the intervention is cost-effective for a range a values placed on a unit improvement in outcome compared to the waiting list control group.

### Monitoring

A Trial Management Group consisting of the clinical (BIS) and research teams (MF, JG/[name]) manage the everyday conduct of the trial through monthly face-to-face meetings and interim secure email contact. A Trial Advisory Group meets six monthly and consist of the clinical and research teams, the trial economist and statistician, academics (with expertise in complex interventions and palliative care RCTs), respiratory and oncology specialists, NHS managers, patients and carers.

### Approvals and trial registration

Ethical approval was obtained from the Cambridgeshire 2 Research Ethics Committee (08/H0308/157) and R&D approval and sponsorship from Addenbrooke's Hospital, Cambridge University Hospitals NHS Foundation Trust (A091322): current protocol version v5 110810. The trial is registered with http://ClinicalTrials.gov (NCT00678405) and Current Controlled Trials (ISRCTN04119516).

## Discussion

This is the first evaluation of an intervention for breathlessness in advanced disease to have followed the MRC framework; only recently has the framework been used in a palliative care setting [34]. It is also one of the very few trials in palliative care to propose the use of fast track methodology [20,34,35], and the first, as far as we are aware, to combine this with single-blinding (other than our Phase II trial [20]).

The Phase III protocol described here was developed based on our Phase II pilot trial [20]. One limitation of this is that the pilot focused only on patients with COPD. The reason for this was that COPD patients made (and continue to make) up the largest group of patients referred to BIS and existing studies of breathlessness interventions had focused on patients with malignancies. Funding was sought for a Phase II trial with patients with malignancies but was unsuccessful. Thus the methods outlined here for Phase III have not been tested on patients with malignant conditions.

A further limitation of this Phase III study may be that although some outcome measures were revised as a result of Phase II, the new measures adopted for Phase III were not subjected to formal piloting, nor were the economic evaluation measures i.e. EQ-5D and CSRI.

The MRC framework has provided a useful structure for the systematic development and evaluation of BIS [3,10,20,21], however, as Booth [36] has commented, the length of time for completion of the framework is considerable. The development work for the Pre-Clinical Phase began in 1998 and Phase III is due for completion in 2012. In this time there will have been changing contextual factors that will need to be considered and accounted for in terms of their impact on both the development of the service and the outcome of its evaluation. Campbell et al (2007) noted that the setting in which an intervention is given must be understood before the intervention can be used elsewhere [37]; this will be particularly important as the evaluation of BIS moves into Phase IV.

The results of this Phase III trial will therefore provide evidence of the effectiveness and cost-effectiveness of BIS, inform the long term development of the service and its implementation in other centres nationally and internationally, as well as adding to methodological developments in palliative care research and the development and evaluation of complex interventions.

## List of abbreviations

BIS: Breathlessness Intervention Service; RCT: randomised controlled trial; COPD: chronic obstructive pulmonary disease; MRC: Medical Research Council; NRS: numerical rating scale; CSRI: Client Services Receipt Inventory.
